### Primary outcomes

The study will assess three primary outcomes:

(I)Participant-level feasibility is assessed by screening completion rates of participants who provided informed consent. The outcome is defined as completion of the structured questionnaire, performance of blood pressure measurement and PoC-testing for dyslipidemia and HbA1c. The study aims for an overall completion rate ≥ 70% based on the reported use of primary care screenings and prospective feasibility on the national level in Germany.(II)Implementation outcomes from the pharmacy perspective are evaluated for the implementation domains acceptability, feasibility, and sustainability. The outcome is evaluated using validated instruments, including the Acceptability of Intervention Measure (AIM), the Feasibility of Intervention Measure (FIM), and the Normalization Measure Development Questionnaire (NoMad) to assess sustainability (Supplementary Tables 1 and NoMad Questionnaire) [16–19]. These instruments use standardized self-administered questionnaires completed by pharmacy staff that are rated on Likert scales. Validated German versions will be used. For each domain, the outcome criterion is defined by a null hypothesis assuming a median Likert-scale score ≤ 3. Rejection of the null hypothesis will be interpreted as evidence of sufficient implementation performance under routine practice conditions.(III)The medical screening yield is quantified by the number needed to screen (NNS) to identify at least one previously unknown or insufficiently managed CKM syndrome risk factor. These are defined as non-HDL cholesterol ≥ 5.7 mmol/L for known dyslipidemia or lipid-lowering therapy, HbA1c ≥ 8.5% in participants with known diabetes mellitus, positive albuminuria test without RASi or SGLT2i therapy in participants with CKD, or blood pressure ≥ 140/80 mmHg for participants with known hypertension. A NNS ≤ 5 will be considered as indicative of a clinically meaningful detection efficiency of the multi-parametric screening approach. Further, a NNS between 5 and 10 will be considered an exploratory finding indicating the need for potential refinement or modification of the screening strategy. An observed NNS > 10 will be interpreted as an unfavorable feasibility outcome under routine practice conditions.

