An NNS of ≤ 5 was predefined as a pragmatic threshold for clinically meaningful detection efficiency. This threshold reflects the identification of one previously unknown or insufficiently managed actionable risk factor in 20% of screened at-risk individuals. Although this is not directly comparable to outcome-based NNS estimates from established screening programs, it is expected to correspond to a downstream NNS to prevent one clinical event of approximately 100–150, assuming that detected abnormalities trigger evidence-based treatment with numbers needed to treat of around 20–30. Against this background, and considering that accepted screening programs often operate with substantially higher outcome-based NNS values, an NNS ≤ 5 was considered a clinically relevant benchmark for this pilot study [20].

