Implementation outcomes will be analyzed separately for each implementation instrument and domain. AIM, FIM, and NoMad assess conceptually distinct implementation constructs, including acceptability, feasibility, and normalization/sustainability. Therefore, no combined implementation score or omnibus test will be used. For each domain, median Likert-scale scores and interquartile ranges will be reported. In addition, one-sided one-sample Wilcoxon signed-rank tests will be used to assess whether domain scores exceed the neutral midpoint of the scale, using the null hypothesis that the median domain score is ≤ 3. Given the exploratory nature of this pilot implementation study and the domain-specific interpretation of implementation outcomes, no formal multiplicity adjustment is planned. Results will be interpreted separately by domain and in the context of the overall implementation pattern.

The unadjusted NNS will be calculated as the number of participants with completed screening divided by the number of participants with at least one previously unknown or insufficiently managed CKM risk factor identified during screening. For primary outcome, a pre-specified PPV-adjusted NNS will be calculated using the positive predictive value estimated among screen-positive participants undergoing confirmatory testing at the study center. Participants without available confirmatory testing will not be included in the estimation of the PPV. Stratified NNS according to pharmacy-prompted or self-referral recruitment will be further reported.

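### The NNS verdict bands sit beside a definition based on screening findings, while the analysis section makes the PPV-adjusted NNS primary; the article never ties the bands to it

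*Protocol article*

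**What the plan says.** Four places in the protocol article bear on this.

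- **Primary outcomes, item III, definition.** "The medical screening yield is quantified by the number needed to screen (NNS) to identify at least one previously unknown or insufficiently managed CKM syndrome". The criteria that follow are cut-offs on screening measurements in people with a known condition. Neither confirmatory testing nor PPV appears.
- **Primary outcomes, item III, decision rule.** For the favourable band, "A NNS ≤ 5 will be considered as indicative of a clinically meaningful detection efficiency of the multi-parametric screening approach". For the middle band, "a NNS between 5 and 10 will be considered an exploratory finding". For the unfavourable band, "An observed NNS > 10 will be interpreted as an unfavorable feasibility outcome under routine practice conditions". The bands are stated once, here.
- **Primary outcomes, rationale paragraph.** "This threshold reflects the identification of one previously unknown or insufficiently managed actionable risk factor in 20% of screened at-risk individuals". On the downstream effect, "it is expected to correspond to a downstream NNS to prevent one clinical event of approximately 100–150", using numbers needed to treat of 20 to 30.
- **Sample size and statistical analysis.** The unadjusted NNS is completed screenings divided by participants in whom screening found at least one qualifying factor. Then: "For primary outcome, a pre-specified PPV-adjusted NNS will be calculated using the positive predictive value estimated among screen-positive participants". The PPV comes from those confirmed at the study center.

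Missing data sets the denominator of the primary NNS analysis (completed screenings only) without saying whether that analysis is adjusted. The Discussion lists the NNS and the PPV as separate quantities.

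**The concern.** The definition and the bands in item III describe a count of screening findings, which is the quantity the analysis section labels unadjusted. The analysis section then gives the primary role to a different quantity and does not mention the bands. No sentence says which of the two NNS values the bands judge.

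The bands are the only decision rule for this primary outcome, and Limitations makes sufficient diagnostic yield a condition for a larger study. PPV cannot exceed 1, so the unadjusted NNS is always at least as favourable as the adjusted one. A report that follows item III to the letter could set the unadjusted value against the cut-off of 5 and call the yield clinically meaningful, when the value named for the primary outcome falls in a less favourable band.

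**Working it through.** **Inputs from the article.** Bands at 5 and 10; 20% as the share behind the cut-off of 5; numbers needed to treat of 20 to 30; 1,000 participants, about 50 per pharmacy; 10 pharmacies near the study center; expected prevalence of 50%; 20% attrition.

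**Assumptions.** The article gives no formula for the adjusted NNS and no expected PPV. I take adjusted NNS = unadjusted NNS / PPV, which is the natural reading, with unadjusted NNS = 1 / yield. Yields and PPVs are shown over a range.

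**Step 1: reproduce the article's figures.**
- Cut-off: 1 / 0.20 = 5.
- Downstream: 5 × 20 = 100 and 5 × 30 = 150.
- Confirmatory sample: 10 × 50 = 500; 500 × 0.5 = 250; 250 × 0.8 = 200.

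All agree with the text.

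**Step 2: which NNS does the rationale fit?** An NNS of 5 means 20% under either definition: 20% with a finding, or 20% with a confirmed factor. The downstream step is more selective, because treatment benefit accrues only to true factors. If the 5 were an unadjusted NNS, the downstream figure would be 5 / PPV × (20 to 30):
- PPV 0.8: 125 to 188
- PPV 0.6: 167 to 250
- PPV 0.5: 200 to 300

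The printed 100 to 150 holds for confirmed factors, or for findings only if PPV = 1. The rationale therefore supports the adjusted NNS.

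**Step 3: where do the two NNS values fall in different bands?** The adjusted NNS exceeds 5 when PPV < 0.20 / yield, and exceeds 10 when PPV < 0.10 / yield.

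| Assumed yield | Unadjusted NNS | Leaves the ≤ 5 band if PPV below | Exceeds 10 if PPV below |
|---|---|---|---|
| 50% | 2.0 | 40% | 20% |
| 30% | 3.3 | 67% | 33% |
| 25% | 4.0 | 80% | 40% |
| 20% | 5.0 | 100% | 50% |

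The 50% row uses the article's expected prevalence as the yield. In the article that figure gives the number with an indication for confirmatory testing, so the share with an unrecognised or poorly controlled factor may be lower.

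**Step 4: is a one-band difference larger than sampling error?** Take yield 25% and PPV 60%, with 1,000 screened and 200 confirmed, ignoring clustering by pharmacy.
- Unadjusted: 4.0; SE of the log = √(0.75/250) = 0.0548; 95% CI 3.6 to 4.5.
- Adjusted: 4.0 / 0.6 = 6.7; SE of the log = √(0.75/250 + 0.4/120) = 0.0796; 95% CI 5.7 to 7.8.

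The intervals lie in different bands.

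**Step 5: precision at the boundary.** At yield 50% and PPV 40%, the product is 0.200 with SE 0.200 × √(0.5/500 + 0.6/80) = 0.0184. The interval for the product is 0.164 to 0.236, so the adjusted NNS is 5.0 with 95% CI 4.2 to 6.1.

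**The case against.** The strongest reply is that the analysis section already makes the choice. It labels one quantity unadjusted, names the other for the primary outcome and calls it pre-specified. An outcomes section that names a measure and a statistics section that operationalises it is ordinary layout. Read together, the bands judge the primary NNS, which is the adjusted one, and that is the more conservative choice. This largely stands. A reader might infer that the choice is left open until the data are seen. The text does not support that, because presenting the unadjusted NNS as primary would go against the analysis section. What remains is that item III is worded on screening measurements and an observed NNS, and neither the analysis section nor Missing data links the adjusted NNS back to the bands.

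A reader might also take the rationale paragraph as a further contradiction, since 20% of screened individuals sounds like a count of findings. It is not one: as Step 2 shows, the 20% fits either NNS and the downstream figure favours confirmed factors.

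Third, it is tempting to say that the two NNS values give opposite verdicts. On the article's own 50% this is not shown: both are at or below 5 for every PPV of 40% or more, and a reversal from ≤ 5 to above 10 needs a PPV below 20%. Most of the plausible damage is a shift of one band, to a finding classed as exploratory.

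Finally, an analysis plan that is not shown may settle the matter, and the interval method belongs there. The second half stands, so the interval is a preference and not a fault. An analysis plan that names the adjusted NNS would still leave the published item III to be aligned.

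**Conclusion.** The mismatch is real and limited. The analysis section is best read as choosing the PPV-adjusted NNS, but the section that defines the outcome and holds the decision bands does not follow it. An unadjusted value could be judged against bands meant for the adjusted one, always to its advantage or at no loss.

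How much this matters depends on yield and PPV, neither of which is known. At a yield of 50% the favourable verdict is robust unless the PPV falls below 40%. At yields of 20% to 30% a moderate loss of PPV is enough to move the result by one band. The thresholds rest on dividing by PPV, and the intervals on independent estimates without clustering. Because a primary outcome's verdict is affected and the remedy is wording, the change should be made.

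**What to change.** In item III of Primary outcomes, state that the three bands are applied only to the PPV-adjusted NNS, give its formula, and say that the unadjusted NNS is descriptive and carries no verdict. In the rationale paragraph, make clear that the 20% means participants with a confirmed risk factor. Under Missing data, name the adjusted NNS as the primary NNS analysis. Preferably, report it with a 95% confidence interval that carries the uncertainty of both the yield and the PPV, by the delta method or bootstrap.

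This costs a few sentences and one calculation, with no further data. The price is a headline NNS that is less favourable and less precise than the unadjusted one.

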**Fig. 1 Fig1:**
[figure not shown]
Flow chart of study recruitment, testing and follow-up. GP, General Practitioner; PoC-Test, Point-of-Care-Test; HDL, high-density lipoprotein; DM, Diabetes mellitus; Obesity defined as (BMI ≥30kg/m² or waist circumference ≥ 88cm for women or ≥ 102cm for men); * if confirmatory testing is not feasible at the GP, participants can conduct confirmatory testing at the study center

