### Sample size and statistical analysis

The planned sample size of 1000 participants allows for reliable estimation of key outcomes with 95% confidence intervals with an estimation error of approximately ± 5%. With an expected prevalence of 50% of risk factors and 10 pharmacies in the region of the study center, we expect 250 participants with indication for confirmatory testing at the study center. At an expected attrition of 20%, 200 participants should complete confirmatory testing. This allows for determination of false-positive rates and test specificity with acceptable precision (± 10%). Attrition in the GP-confirmatory testing arm is expected to be higher, but will be minimized through repeated digital or telephone prompts and, if necessary, invitation for testing at the study center. Statistical analysis will be descriptive, using frequency tables, means (± standard deviation), medians (± interquartile range) for Likert-Scale analysis, and proportions with 95% confidence intervals. Diagnostic metrics (sensitivity, specificity, PPV, NPV) will be determined. Sensitivity of the PoC test can be assessed based on the results from the confirmatory testing. Scale scores for implementation metrics will be calculated as the mean of the respective items, with higher values indicating greater agreement and lower values indicating greater disagreement.

Feasibility and clinical outcomes will be summarized overall and, where appropriate, descriptively at pharmacy level. Pharmacy-level summaries will include recruitment numbers, screening completion rates, confirmatory testing uptake, diagnostic yield, and implementation scores. Baseline pharmacy characteristics will be used to contextualize variation across pharmacies, whereas pharmacy-level implementation process metrics will be interpreted as outcomes of the implementation process. Given the limited number of participating pharmacies, these analyses will be exploratory and hypothesis-generating. Confirmatory inference regarding pharmacy-level predictors is not planned.

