### Missing data

Missing data will be reported for each variable individually and will be transparently documented for all variables included in the analysis, and reported as part of the descriptive results. Within the electronic case report form (eCRF), participants are given the option to select an “unknown” category where applicable, thereby allowing explicit capture of non-available responses at the point of data entry. Responses documented as “unknown” will be reported descriptively and treated as missing for analyses requiring classification of a risk factor as previously known, unknown, controlled, or insufficiently managed.

No formal imputation of missing data is planned given the exploratory character of this pilot implementation study.

Participants without available confirmatory testing for the respective parameter will not be included in parameter-specific PPV or diagnostic accuracy calculations. Uptake of confirmatory testing and missing confirmatory results will be reported descriptively. For implementation questionnaires, domain scores will be calculated only if sufficient item-level data are available for the respective domain. Otherwise, the domain score will be treated as missing. No item-level imputation is planned.

For the participant-level completion rate, participants who provide informed consent and start the screening procedure will remain in the denominator; participants with incomplete subsequent screening procedures will be counted as not completed. For the primary NNS analysis, only participants with completed screening procedures will be included in the denominator. Participants with incomplete screening procedures will therefore not contribute to the NNS analysis, but their number will be reported through the completion-rate outcome.

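### The PPV that adjusts the primary NNS comes from a different set of participants than the NNS numerator, so an adjusted NNS near 5 or 10 can fall in the wrong band

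*Protocol article*

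**What the plan says.** Primary outcome III in the protocol article is the NNS to find at least one previously unknown or insufficiently managed risk factor. Three bands are set in advance: up to 5 is clinically meaningful, 5 to 10 is exploratory, and above 10 is unfavorable.

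Under Sample size and statistical analysis, the unadjusted NNS is completers divided by participants with at least one such factor. For the primary outcome a PPV-adjusted NNS is then calculated, "using the positive predictive value estimated among screen-positive participants undergoing confirmatory testing at the study center". No formula is given, and the PPV is not restricted to participants in the numerator.

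The two sets are defined in different places:

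- **Numerator (Primary outcomes):** for albuminuria in known disease, a "positive albuminuria test without RASi or SGLT2i therapy in participants with CKD"; for known hypertension, blood pressure at or above 140/80 mmHg.
- **Screen-positive (Confirmatory testing):** any positive albuminuria test, whatever the therapy; systolic at or above 140 and/or diastolic at or above 90 mmHg.
- **Unknown prior status (Missing data):** treated as missing when a factor is classified as known, unknown, controlled or insufficiently managed.

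Missing data adds that participants without a confirmatory result for a parameter "will not be included in parameter-specific PPV or diagnostic accuracy calculations". On testing site, Sample size and statistical analysis says "Attrition in the GP-confirmatory testing arm is expected to be higher", and the Fig. 1 footnote says "if confirmatory testing is not feasible at the GP, participants can conduct confirmatory testing at the study center".

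**The concern.** Multiplying a count by a PPV turns it into an estimate of true positives only if the PPV describes the people counted. Here the count is of unknown or insufficiently managed factors, while the PPV is an average over everyone who was screen-positive and tested at the center. Participants outside the numerator may confirm more often or less often than those inside it. Either way, their confirmation rate is carried into the yield.

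This adjusted figure is the one named for the primary outcome, and it is read against fixed cut-offs. The Limitations section makes a larger study depend on sufficient diagnostic yield, so the band matters.

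**Working it through.** **The plan's own figures.** The article states "The planned sample size of 1000 participants allows for reliable estimation of key outcomes with 95% confidence intervals", with 50% expected prevalence and 10 of 20 pharmacies in the center's region.

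- 1,000 × 0.50 × 10/20 = 250, which matches "we expect 250 participants with indication for confirmatory testing at the study center".
- 250 × (1 − 0.20) = 200, which matches "At an expected attrition of 20%, 200 participants should complete confirmatory testing".

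The PPV would therefore rest on about 200 of 500 expected screen-positives (40%).

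**Where the sets differ, on the article's definitions.**

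| Group | Screen-positive (can enter PPV) | In NNS numerator on that factor |
|---|---|---|
| Known CKD, albuminuria, on RASi or SGLT2i | yes | no |
| Prior status unknown, value above threshold | yes | no (missing) |
| Known hypertension, systolic < 140, diastolic 80–89 | not on blood pressure | yes, if 140/80 means either limit |
| Known hypertension, systolic ≥ 140, diastolic < 80 | yes | no, if 140/80 means both limits |

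The non-HDL cholesterol threshold and the HbA1c threshold for known diabetes agree in both places.

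**Formula (assumed, since the article gives none).** Adjusted NNS = completers / (qualifying × PPV). If w is the share of screen-positives who are in the numerator, then PPV as written = w × PPV(numerator) + (1 − w) × PPV(others). The matched version uses PPV(numerator) alone.

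**Main illustration.** Assumed: 1,000 completers, 300 qualifying, 60% of them confirmed, other screen-positives confirmed at 90%.

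- Matched: 300 × 0.60 = 180; 1,000/180 = 5.56.
- Pooling 100 others: PPV = (180 + 90)/400 = 0.675; 1,000/(300 × 0.675) = 4.94.
- Pooling 50 others: PPV = (180 + 45)/350 = 0.643; NNS = 5.19, with no crossing.
- To reach 5 the PPV must be 200/300 = 0.667. Solving (180 + 0.9k)/(300 + k) = 0.667 gives k = 20/0.2333 = 85.7, so 86 people.

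If the matched result lies closer to the cut-off, fewer are needed. With 300 qualifying at 65%, the matched NNS is 1,000/195 = 5.13. Adding 22 others at 90% gives PPV 214.8/322 = 0.667 and an NNS just under 5.0.

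**Other assumed inputs (1,000 completers, 500 screen-positive).**

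| w | PPV numerator / others | PPV as written | NNS as written | NNS matched |
|---|---|---|---|---|
| 0.9 | 0.60 / 0.90 | 0.63 | 3.53 | 3.70 |
| 0.6 | 0.60 / 0.90 | 0.72 | 4.63 | 5.56 |
| 0.5 | 0.90 / 0.60 | 0.75 | 5.33 | 4.44 |
| 0.4 | 0.45 / 0.80 | 0.66 | 7.58 | 11.11 |

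The last three rows change band, and not all in the same direction. No case tried at w = 0.9 changed band, and none can if w = 1 or the two PPVs are equal.

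**Counted but not referred on blood pressure.** Reading 140/80 as either limit, 300 referred qualifying participants plus 50 with diastolic 80–89, all at PPV 0.60, give 1,000/(350 × 0.60) = 4.76. Without the 50 the NNS is 5.56. The 50 take on a PPV to which they may have contributed no blood pressure confirmation. If instead 100 of the 300 are such cases and would confirm at 30%, true positives are 200 × 0.60 + 100 × 0.30 = 150 and the NNS is 6.67 against 5.56. That is a bias, but both values lie in the 5–10 band.

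**Room before the lower cut-off.** The PPV needed for NNS ≤ 5 is 0.20 divided by the numerator's share of completers: 0.40 at 50%, 0.50 at 40%, 0.667 at 30%, 0.80 at 25% and 1.00 at 20%.

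**The case against.** The strongest reply is that the over-inclusion is narrow. The lipid and known-diabetes HbA1c criteria agree, and treated CKD with albuminuria may be a small group: the Background puts undetected CKD at 49–84% of cases, which limits known CKD. The 86 people needed in the main illustration would be over a fifth of its screen-positives (86/386 = 22%). If all of the planned 50% were in the numerator, the unadjusted NNS would be 2.0, and only a PPV below 0.40 would take it out of the best band. This stands: a band change is a possibility near a cut-off, not an expectation.

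The article's brevity is a weaker reply. Interval methods and sensitivity analyses can be left to an analysis plan, but the article itself fixes the source of the PPV, and that source does not match the numerator.

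A reader might infer more than the documents support:

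- **That the plan flatters the result.** The third row of the second table shows the opposite, and the article gives no PPVs from which to tell.
- **That diastolic 80–89 cases are never confirmed.** Any one positive parameter triggers referral, and all screened parameters are then reassessed. The gap is only that this finding alone does not trigger referral.
- **That parameter-specific PPVs are multiplied into the NNS.** The article does not say so. Its wording reads more naturally as one participant-level PPV, and the parameter-specific ones fit the exploratory diagnostic metrics.
- **That leaving out GP results is an error.** One standardized reference at the study center is a defensible choice, and distant participants come there when GP testing is not feasible or on invitation if necessary. A sensitivity analysis is enough.

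**Conclusion.** The concern holds. The primary adjusted NNS applies a PPV from all screen-positive participants tested at the center to a numerator that the article defines differently for treated albuminuria, unknown prior status and blood pressure. The adjusted NNS is biased where confirmation rates differ between these groups. The documents fix neither the size nor the direction of the bias.

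With assumed inputs the shift runs from negligible (3.53 against 3.70) to a change of band (4.94 against 5.56; 7.58 against 11.11; in reverse, 5.33 against 4.44). A band change needs unequal PPVs and a result near 5 or 10. All PPVs, numerator shares and the adjustment formula used here are assumptions. The rule should be corrected before results are seen, because the outcome is primary, its bands are preset and the correction needs no new data.

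**What to change.** 1. Define one participant-level PPV: among NNS-qualifying participants with study-center confirmatory results, the proportion in whom at least one factor that qualified them is confirmed.
2. State the formula: adjusted NNS = completers / (qualifying × PPV). Weight the PPV to the triggering-parameter mix of all qualifying participants, not of all 1,000 screened, because the PPV multiplies only those who qualify.
3. Carry the uncertainty of both the yield and the PPV into the confidence interval, for example by bootstrapping pharmacies.
4. Add a sensitivity analysis that includes available GP confirmations. Keep the unadjusted NNS beside the adjusted one, as already planned.
5. The authors must reconcile the 140/80 and 140 and/or 90 criteria so that everyone counted in the numerator is eligible for confirmation on that factor. Until then, report separately those counted but not referred on it, since restricting the PPV does not supply their missing results.

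The cost is wording, modest extra analysis and a smaller PPV sample. If 60% of the 200 tested were numerator members (assumed), 120 would remain. At a PPV of 0.70 the 95% half-width, 1.96 × √(0.70 × 0.30/n), grows from 6.4 points at n = 200 to 8.2 at n = 120, before any allowance for weighting or clustering.

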## Methods/design

### Study aim and design

The APOSCREEN-1 study is a single-arm clinical trial conducted in community pharmacies located in the federal state of Schleswig-Holstein, Germany. The study aims to assess the feasibility and diagnostic yield of a multi-parametric, pharmacy-based, risk-adapted point-of-care (PoC) screening for CKM syndrome risk factors. It follows a two-step approach: first, a pragmatic point-of-care screening in pharmacies is conducted to triage patients with high cardiovascular risk who may benefit strongly from further diagnostic work-up. In a second step, these patients undergo detailed confirmatory testing and receive guideline-based therapeutic recommendations. Ethical approval has been obtained from the local institutional review board (AZ D616/25).

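### The primary PPV-adjusted NNS silently assumes that screen-positives who are never re-tested would be confirmed as often as those who attend; the assumption should be stated and bounded.

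*Protocol article*

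**What the plan says.** The Study aim and design section describes the screening in two stages ("It follows a two-step approach"): a pharmacy triage, then confirmatory work-up of those who screen positive. Under Sample size and statistical analysis, the unadjusted NNS divides completed screenings by participants with at least one qualifying finding. The version designated for the primary outcome is then calculated "using the positive predictive value estimated among screen-positive participants undergoing confirmatory testing at the study center". The rule for everyone else is explicit: "Participants without available confirmatory testing will not be included in the estimation of the PPV".

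The Missing data section repeats the exclusion for each parameter (such participants "will not be included in parameter-specific PPV or diagnostic accuracy calculations") and adds: "No formal imputation of missing data is planned given the exploratory character of this pilot implementation study". Uptake is handled outside the estimate: "Uptake of confirmatory testing and missing confirmatory results will be reported descriptively".

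The same statistical section gives the planning figures: 50% of participants with a positive finding, 250 positives from the ten pharmacies near the study center, and then "At an expected attrition of 20%, 200 participants should complete confirmatory testing". It expects higher attrition, without a figure, where confirmation is left to the GP. The Primary outcomes section sets the reading of the NNS: 5 or below is favourable, 5 to 10 exploratory, above 10 unfavourable.

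**The concern.** Participants are invited to confirmatory testing, so attendance is their own decision. How abnormal the screening result was could plausibly influence both whether they come and whether the finding is confirmed. A PPV from attenders alone carries over to all positives only if attendance is unrelated to confirmation. The article relies on that without stating it.

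Step-one and step-two dropouts are also treated differently. A participant who starts the screening but does not finish counts as a failure in the completion rate. A screen-positive who never has the second test simply leaves the PPV. No other primary outcome picks this up: completion ends with the questionnaire, blood pressure, lipids and HbA1c, and the implementation outcome is a staff questionnaire.

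At stake is how the NNS is read against its marks of 5 and 10. The Limitations section makes a larger study conditional on sufficient diagnostic yield.

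**Working it through.** **Inputs from the article.** 1,000 participants; 50% positive; 10 of 20 pharmacies near the study center; 20% attrition; marks at NNS 5 and 10.

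**Assumptions.** The article gives no PPV, so 60% is used, with other values where shown. It prints no formula for the adjusted NNS, so the natural reading is taken, with q the positive share and p the PPV among attenders:

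NNS = completed / (positives × p) = 1/(q × p).

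One uptake figure, a, is applied to all positives. The article gives no rate for the GP arm.

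**The plan's own figures.** 1,000 × 0.50 × 10/20 = 250, and 250 × 0.80 = 200. Both reproduce. The PPV would thus come from about 200 of the 500 expected positives (40%).

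**General form.** If non-attenders would be confirmed at rate r:

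NNS = 1/(q × [a × p + (1 − a) × r]).

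The planned figure is the case r = p, in which a cancels. Setting r = 0 or r = 1 gives the bounds.

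**Results at q = 0.50, p = 0.60**

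| Uptake a | Planned (r = p) | None confirmed (r = 0) | All confirmed (r = 1) |
|---|---|---|---|
| 80% | 3.33 | 1/(0.5 × 0.48) = 4.17 | 1/(0.5 × 0.68) = 2.94 |
| 50% | 3.33 | 1/(0.5 × 0.30) = 6.67 | 1/(0.5 × 0.80) = 2.50 |
| 20% | 3.33 | 1/(0.5 × 0.12) = 16.67 | 1/(0.5 × 0.92) = 2.17 |

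Precision does respond to uptake. From PPV uncertainty alone, the 95% interval for the planned NNS is 2.99 to 3.76 with 200 confirmed (80%) and 2.72 to 4.31 with 50 (20%).

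**Where the r = 0 bound crosses a mark**
- Uptake, at q = 0.50 and p = 0.60: NNS 5 at a = 1/(5 × 0.5 × 0.6) = 67%; NNS 10 at a = 1/(10 × 0.5 × 0.6) = 33%.
- Attender PPV, at q = 0.50 and a = 0.80: NNS 5 at p = 1/(5 × 0.5 × 0.8) = 50%. At p = 40% the planned NNS is 5.0 and the bound is 6.25.
- Positive share, at p = 0.60 and a = 0.80: NNS 5 at q = 1/(5 × 0.8 × 0.6) = 42%.

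**Selective attendance, in either direction (all rates assumed).** Let half the positives be borderline (PPV 40%) and half clear (PPV 80%), a true PPV of 60%, with 80% attending overall.
- Clear cases attend more (95% against 65%): observed PPV = (0.5 × 0.65 × 0.4 + 0.5 × 0.95 × 0.8)/0.8 = 63.75%. At q = 0.50 the NNS reads 3.14 instead of 3.33.
- Borderline cases attend more (rates reversed): observed PPV = (0.5 × 0.95 × 0.4 + 0.5 × 0.65 × 0.8)/0.8 = 56.25%. At q = 0.50 the NNS reads 3.56 instead of 3.33.

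**The case against.** The strongest reply is that nothing moves on the plan's own figures: with 50% positives, 20% attrition and a PPV of 50% or more, even counting every non-attender as unconfirmed leaves the NNS at or below 5. That stands, and it limits the weight of the point.

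A reader might go further in four ways, and the documents support none of them.

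- **That the planned NNS is biased low and would turn a failure into a pass.** Such a case can be built: with the first attendance pattern above and 32% positive, a true NNS of 1/(0.32 × 0.60) = 5.21 reads 1/(0.32 × 0.6375) = 4.90. But 32% replaces the plan's 50%, and every attendance and confirmation rate in it is assumed. The shift of 3.75 points is also less than half the sampling half-width of about 8 points with 1,000 × 0.32 × 0.5 × 0.8 = 128 confirmed. The bias could equally run the other way: the Limitations section itself names healthy volunteer bias, and health-conscious people with borderline values may attend more readily.
- **That the result is the same whatever the uptake.** This holds only for the point estimate at a fixed observed PPV. The interval widens as uptake falls, and the observed PPV itself moves if attendance is selective.
- **That poor uptake is hidden.** Uptake is to be reported, also by pharmacy, an unadjusted NNS is defined, and prompts are planned in the GP arm. These inform the reader but do not enter the primary figure.
- **That success should require the worst-case figure to pass as well.** Counting non-attenders as unconfirmed measures completion of the pathway, whereas the outcome is defined as screening yield. If GP-tested positives were also treated as unverified, the figure would be 1,000/(200 × 0.6) = 8.3 with attendance exactly as planned, and 1,000/200 = 5.0 even at a PPV of 100%.

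Finally, weighting and sensitivity analyses may sit in an analysis plan that is not shown. Their absence from the article is therefore not the point. The point is the stated exclusion rule and the assumption that it carries.

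**Conclusion.** The point holds in limited form. The article fixes a complete-case PPV for a primary outcome, and the resulting NNS is valid for all positives only if non-attenders would be confirmed as often as attenders. That assumption is not stated, and the direction of any error is unknown.

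At the planned 50% positives and 80% uptake, with an assumed PPV of 60%, the NNS is 3.3 with bounds of 2.9 and 4.2, all within the favourable band. The interpretation depends on non-attenders if uptake falls below about 67% at that PPV, if attender PPV is below 50% at the planned uptake, or if the positive share drops below about 42%. These figures rest on the inferred formula, the assumed PPV and a common uptake across both arms. Zero confirmation among non-attenders is a bound, not an expectation. This is a worthwhile, cheap improvement rather than something that must be corrected.

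**What to change.** In the NNS paragraph of Sample size and statistical analysis:

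1. Print the formula for the adjusted NNS and state the assumption about screen-positives who are not re-tested.
2. Standardise the PPV to all screen-positives, by post-stratification or inverse-probability weights, using screening data already in the eCRF: which tests were positive, how many, and the distance above the cut-off where the test is quantitative. For the semi-quantitative home albuminuria test, use the result category only.
3. Beside it, report the NNS with positives tested nowhere counted first as not confirmed and then as confirmed.
4. State how GP-tested positives are handled, and do not count them as untested.
5. If the bounds straddle 5 or 10, say that the interpretation depends on non-attenders. Do not make the worst-case bound a condition for calling NNS ≤ 5 met.

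The cost is a few sentences, a little more analysis and slightly wider intervals. No new data are needed. It should be settled before the confirmatory results are analysed, so that the choice cannot follow the result.
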